### Focus groups with patient participants

The following types of patients will be represented among those we interview: (1) patients who were clinician-referred and received A/C services; (2) patients who received A/C without a clinician referral; and (3) comparable CMP patients who have not received A/C (including those referred who did not follow through). We will use data collected through Phase 1 EMR analyses and out-of-plan surveys to identify these types of patients for sampling. We anticipate holding multiple focus groups for each category of participants. Those who received acupuncture and chiropractic care will be recruited for separate focus groups.

Focus groups are an efficient mechanism for investigating how people conceptualize, experience, and talk about issues, for examining a range or consensus of experiences, and for collecting qualitative data from many individuals in a short time. Focus groups will be audio-recorded and consist of 6-12 participants, an optimal size range for discussing behaviors and experiences [73]. Each patient focus group will address the three main topics described above. As part of that process, we will explore two additional issues related to the decision-making process as shown in the model in Figure 1: factors that prompt individuals to seek and, once initiated, continue or discontinue A/C care, and reasons for deciding to seek care with or without primary care provider concurrence. The first wave focus group results will be used to refine the draft Phase 3 questionnaires. Second wave focus groups of prior A/C users will be asked to complete the draft questionnaires prior to focus group attendance and be prepared to advise researchers on domains or questions relevant to their use of A/C services not covered in the questionnaire, as well as to comment on their understanding of the questions we designed. We will not alter questions that are part of validated instruments, but we will use the feedback to refine our overall assessment battery and to adjust items that we have created based on first-wave focus groups.

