#### Phase 3: Prospective Cohort Study to Evaluate Outcomes Associated with the Use of A/C Services

To conduct a prospective cohort study of carefully matched A/C and non-A/C patients, we will use clustering and matching methods identified in Phase 1. These matching approaches will be refined by Phase 2 qualitative findings and augmented by additional, directly assessed, patient-reported baseline data. We will follow matched patients to examine outcomes, which will include EMR (service utilization and health care costs) and patient-reported clinical, psychosocial, and QOL outcomes over a one-year prospective timeframe for each patient. We will compare outcomes from the prospective cohort to those found during Phase 1 EMR-only analyses. Specifically, we will conduct the following activities:

1. Set up a weekly surveillance tracking system to identify CMP patients referred for A/C care to allow timely recruitment of these (index) patients and two carefully matched CMP control patients.

2. Coordinate telephone or online assessments for index and comparison patients upon recruitment (baseline; prior to A/C care) and at 1-, 3-, 6-, and 12-month follow-ups.

3. Compare outcomes (clinical and psychosocial/QOL/satisfaction outcomes and health care utilization) and explore health care costs between those receiving A/C and comparison patients not receiving such services, examining relationships between patient characteristics and decisions to use A/C.

4. Conduct comparative and sensitivity analyses between results using methods that rely solely on EMR-derived data (Phase 1) with those supplemented by patient and provider data (Phase 3).

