### Phase 3 participants and recruitment

***Index ***participants (i.e., those with an incident A/C referral, n = 200 acupuncture and 200 chiropractic) and matched ***comparison ***participants in this prospective portion of the study must meet the overall CMP eligibility criteria listed in Table 1 and be able to read and respond to assessment questionnaires. Both index and comparison patients must have had no A/C treatment over the previous six months to ensure that we are prospectively following a new episode of A/C care. We purposefully minimized exclusion criteria to ensure that study findings are as broadly representative of the CMP population as possible.

Health plan members will be recruited over a two-year period through a weekly EMR review to identify CMP patients referred for A/C. Those referred for A/C will be mailed an invitation to the study, including a brochure and letter describing the study, and indicating that a staff member will call soon to tell them more about the study. There will also be a study website where prospective participants can log on to learn more about the study and eligibility or opt out if they so choose. Eligible participants will be guided through the consent process and baseline assessments by an interviewer or online, according to their preferences.

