### Identification of comparison participants

To recruit comparison cases for each participant in our cohort of A/C users, we will identify CMP-patient matches using the clustering/matching approach determined from Phase 1 and refined based on Phase 2 findings. As with Phase 1, participants must have a primary care visit within one month of the index patients' A/C referral so that we know that an opportunity for A/C referral existed. When an index patient enrolls online, the matching process is triggered: those matches will be located, mailed the same informational materials, and invited to enroll online. We will recruit two or more comparison participants for every index participant. A greater number of comparison participants allows a buffer of comparison participants in the event that some report A/C use during the assessment window.

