### Phase 3 Data Analysis

#### Patient-reported outcomes

For the patient-reported outcomes in Phase 3, we will examine differences in baseline measures between participants with and without data at the 1-, 3-, 6-, and 12-month  follow-ups. Variables related to missingness will be included in the main analyses as covariates to reduce bias in the estimates [109,110].

We will use multilevel modeling to examine differences across time in primary (pain intensity/interference/bothersomeness) and secondary patient-reported outcomes between A/C users and matched comparison participants. Two parameters (linear and quadratic slope) will characterize change across time, with linear slope capturing initial rate of change and quadratic slope reflecting the degree to which the change slowed (or increased) over time. Thus, the quadratic model for time (baseline and 1-, 3-, 6-, and 12-month follow-ups) captures nonlinear change across time. Unlike repeated measures analysis of variance, multilevel modeling does not require data at all time points from each subject, so data from all subjects will be included in analyses. Depending upon the distribution, normal, logistic, or Poisson models will be used. Importantly, these analyses can be adjusted using additional information collected from participants during the baseline assessment that we may identify in Phase 2 as influencing A/C decision-making. This will better control for factors not available during comparison patient identification when only EMR data will be available for matching/clustering.

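### Phase 3 enrols by A/C referral but states its comparison by A/C receipt, and gives no clear rule for comparison patients who start A/C or referred patients who do not

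*Protocol article*

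**What the plan says.** All references are to the protocol article.

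**Enrolment is by referral.** In the introduction to Phase 3, activity 1 sets up weekly surveillance "to identify CMP patients referred for A/C care to allow timely recruitment of these (index) patients". *Phase 3 participants and recruitment* defines index participants as "those with an incident A/C referral, n = 200 acupuncture and 200 chiropractic". Activity 2 schedules assessments "upon recruitment (baseline; prior to A/C care) and at 1-, 3-, 6-, and 12-month follow-ups". Receipt of A/C is therefore always a post-baseline event.

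**The contrast is by receipt.** Activity 3 compares outcomes "between those receiving A/C and comparison patients not receiving such services". The multilevel model in *Patient-reported outcomes* (Phase 3 Data Analysis) examines differences "between A/C users and matched comparison participants". *Identification of comparison participants* also calls the index cohort A/C users. *Phase 3 Sample Size* counts the same 200 + 200 as people receiving the services.

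**Changes of status.** For comparison participants who take up A/C, the only provision is: "A greater number of comparison participants allows a buffer of comparison participants in the event that some report A/C use during the assessment window". The document knows that referral and receipt differ. Its Phase 2 focus-group categories include "comparable CMP patients who have not received A/C (including those referred who did not follow through", placed with the patients who did not receive A/C. The Phase 3 sections give no rule for such patients.

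**The concern.** Two definitions of the index group are in use, and they pick out different people whenever a referred patient does not attend. The comparison group has the mirror problem: membership is set at matching, but the buffer suggests that it can be lost later by using A/C.

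Pain that worsens may send a comparison patient to A/C, and pain that settles may lead a referred patient to skip it. Pain severity, interference and bothersomeness are the primary outcomes, so either selection acts on the outcome itself. Removing comparison patients whose pain worsened leaves a group that looks better than the one enrolled, which works against A/C. If it is the improving patients who take up A/C, the bias runs the other way. Matching and baseline covariates balance what was known at the referral date and cannot undo selection on what happened afterwards. The buffer protects the number of comparison patients, not their comparability.

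**Working it through.** **1. The plan's own figures.** *Phase 3 Sample Size* gives SD 2, pre-post correlation 0.5, a 1-unit difference in mean change, two-sided alpha 0.025 and 100 per group.
- SD of change = 2 × √(2 × (1 − 0.5)) = 2.0.
- Standard error = 2 × √(2/100) = 0.283, and 1/0.283 = 3.54.
- Critical value 2.241; power = Φ(3.54 − 2.241) = 0.902 (noncentral t: 0.898). The stated value, slightly over 90%, reproduces.
- Total = 200 + 200 + 2 × 400 = 1,200, as stated.

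The sample size arithmetic is sound. The difficulty lies in who belongs to each group.

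**2. Possible shift from removing comparison patients.** The documents give no crossover rate and no outcome gap, so both are assumed. If a share p is removed and those patients end g BPI points worse than the ones kept, the comparison mean moves by p × g.
- Low end: 0.05 × 0.5 = 0.025 units.
- High end: 0.20 × 1.5 = 0.30 units, or 30% of the planned 1 unit.

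**3. Effect on false-positive rate.** Assume no A/C effect, SD of change 2, 200 index and 400 comparison patients enrolled, and uptake correlated r with a worse pain course. Remove only the comparison users, a share c. The expected spurious difference is 2 × r × φ(z)/(1 − c), where z is the (1 − c) normal quantile; simulation agrees.
- c = 10%, r = 0.2: 2 × 0.2 × 0.1755/0.90 = 0.08 units; type I error 0.039.
- c = 20%, r = 0.4: 2 × 0.4 × 0.2800/0.80 = 0.28 units; type I error 0.247.

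The nominal level is 0.025. In this set-up the bias runs against A/C.

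**4. What an as-enrolled analysis costs.** With uptake u among referred patients and A/C use c among comparison patients, a 1-unit effect becomes u − c. At 200 versus 400 the standard error is 2 × √(1/200 + 1/400) = 0.173. Power = Φ((u − c)/0.173 − 2.241). The rates are assumed.

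| Uptake u | Comparison use c | Diluted effect | Power |
|---|---|---|---|
| 0.9 | 0.1 | 0.8 | 0.991 |
| 0.8 | 0.1 | 0.7 | 0.964 |
| 0.8 | 0.2 | 0.6 | 0.889 |
| 0.7 | 0.2 | 0.5 | 0.741 |
| 0.6 | 0.2 | 0.4 | 0.527 |

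**The case against.** Much of the case on the other side stands.

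- **Removal is not stated.** The article does not say that comparison participants who use A/C are dropped or replaced. Spare unexposed matches would also serve a censored or time-varying analysis. Removal remains the likeliest meaning of a buffer, but it is an inference.
- **No text drops referred non-users.** A reader might infer this from the receipt wording, but the only mention of patients who did not follow through is a Phase 2 focus-group category. It shows that non-uptake was recognised, not that Phase 3 excludes anyone. A handling rule may well stand in a fuller document.
- **There is no contradiction with the all-subjects statement.** A reader might set the buffer against "so data from all subjects will be included in analyses". That clause explains that multilevel models tolerate missed visits. It does not address group membership.
- **Receipt is a legitimate question.** The study asks about real-world use of A/C, and comparing by referral answers a different question. Which one leads is partly a choice of estimand.
- **The problem is partly acknowledged.** The Phase 1 text says that treated or control status depends on the outcome window and that this complicates the analysis. *EMR-related outcomes* carries the Phase 1 issues into Phase 3, but the primary patient-reported outcomes get no such treatment.
- **The magnitude is assumed throughout**, and at its low end it is small.

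These points do not remove the mismatch: the article itself defines one index group by referral in some sections and by receipt in others.

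**Conclusion.** The point holds in a limited form. Phase 3 fixes enrolment and baseline at referral, but words its main contrast and its sample size count by receipt. It implies, without saying so, that comparison patients who use A/C leave the comparison set, and it is silent on referred patients who do not attend. Any grouping or exclusion on behaviour after baseline can bias the primary pain outcomes in either direction, and baseline matching does not correct it.

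The size cannot be known from the document. Under the assumed 5% to 20% removal and 0.5 to 1.5 point gap, it is about 0.03 to 0.30 units against the planned 1 unit. The document does not support the stronger statements that comparison users are to be replaced, that referred non-users are excluded, or that the direction of bias is known.

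**What to change.** 1. Reconcile the wording in the Phase 3 activities, *Phase 3 participants and recruitment*, *Identification of comparison participants*, *Patient-reported outcomes* and *Phase 3 Sample Size*, so that one definition of index and comparison applies throughout.
2. Fix group membership at the referral/matching date and report the analysis of all participants as enrolled. Do not remove or replace comparison participants who later use A/C, and say that referred patients who do not attend stay in the index group for this analysis.
3. Give the receipt-based effect as a companion analysis, labelled as such in advance. Follow comparison participants until A/C start and censor there, with inverse-probability weights built from the baseline and 1-, 3- and 6-month scores. State how referred non-users enter this analysis.
4. Report uptake in both groups: reimbursed A/C from administrative records at each follow-up, and out-of-plan use at 3, 6 and 12 months. Table 5 does not collect out-of-plan use at month 1.

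**Cost.** Rewording and one weighted analysis, using data already in Table 5. The real downside is dilution of the as-enrolled estimate by crossover. At the protocol's alpha of 0.025, planned numbers withstand 80% uptake with 10% comparison use (power about 0.96) but not 60% with 20% (about 0.53). Both pairs of rates are assumptions, which is a further reason to report uptake alongside the estimate. The weighted analysis assumes that the recorded scores capture what drives A/C start between visits.

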### Outcome measures and study instruments

The assessment schedule for standardized questionnaires and delineation of EMR-collected outcomes are shown in Table 5. Patient-reported outcomes are measured in a time frame (1-12 months) consistent with many RCTs and other outcome studies of A/C [19,80,81]. Assessment instruments and domains are consistent with the Initiative on Methods, Measurement, and Pain Assessment in Clinical Trials (IMMPACT) recommendations [82,83]. In addition, we include variables representing patient factors influencing the decision to use CAM [43] (Figure 1 plus others identified in Phase 2) to help refine matches of those who do and do not seek A/C.

**Table 5 T5:** Phase 3 Assessment Schedule

	Assessment Month				
	0	1	3	6	12
**Chronic Musculoskeletal Pain Patient Measures:**					
**Pain and related disability (patient-reported, primary outcomes)**					
Pain Severity (BPI-SF subscale)	√	√	√	√	√
Pain Interference (BPI-SF subscale)	√	√	√	√	√
Pain Bothersomeness (single item)	√	√	√	√	√
**Secondary Outcomes (survey instruments)**					
Overall well-being (Arizona Integrative Outcomes Scale)	√	√	√	√	√
Patient global impression of change		√	√	√	√
Quality of sleep (ISI)	√	√	√	√	√
Work- and activity-related impairment (NHIS questions)	√	√	√	√	√
Depression (PHQ-8)^1^	√	√	√	√	√
Anxiety (GAD-2)^1^	√	√	√	√	√
Quality of Life/health utility index (SF-12)	√	√	√	√	√
Patient satisfaction		√	√		
**Secondary outcomes (health care utilization collected through EMR and administrative records)**					
Overall use of healthcare services and associated costs		EMR^2^	EMR	EMR	EMR
Use of medications (short and long-acting opiates, sedatives, hypnotics, antidepressants)		EMR	EMR	EMR	EMR
Pain-related procedures (injections and imaging)		EMR	EMR	EMR	EMR
Pain-related visits (primary and specialty care)		EMR	EMR	EMR	EMR
ER/urgent care visits		EMR	EMR	EMR	EMR
Adverse events associated with conventional and CAM CMP treatment^3^		EMR	EMR	EMR	EMR
Use of health insurance reimbursed CAM		A^4^	A	A	A
**Patient characteristics and potential moderators (including predisposing, enabling, and need factors associated with A/C use decision from **Figure 1)					
Demographics	√				
Received/seeking pain-related disability compensation	√				
Patient expectations/CAM attitudes	√				
Other characteristics of pain condition (type(s)/duration)	√				
Previous use of acupuncture/chiropractic services (adapted from NHIS survey)	√				
Utilization of non-plan CAM health services & products	√		√	√	√
**Healthcare Provider (Allopaths/Acupuncturists/Chiropractors) Measures:**					
Allopathic provider characteristics and CAM beliefs	√				
Acupuncturist/chiropractic service provided & general practices			√	√	

Note: ^1^depression and anxiety about pain will also be examined as potential moderators of pain outcomes; ^2^EMR = electronic medical record, ^3^participants will also be asked directly about CMP treatment-related adverse events; ^4^A = administrative record;

#### Primary outcomes: Pain and related disability

Two subscales--the 4-item pain severity and the 7-item pain interference subscales--from the short form of the Brief Pain Inventory (BPI-SF)[84,85] will be used to assess pain and related disability. The BPI has sound psychometrics and has been widely adopted for clinical pain assessment, epidemiological studies, and studies of treatment efficacy. We will also include a measure of how bothered participants are by their pain. This instrument uses a 0 to 10 scale of "symptom bothersomeness, " where 0 represents "not at all bothersome" and 10 is "extremely bothersome." This question has been frequently used in studies of back pain [18,19,86] and shown to have adequate construct validity [87].

#### Secondary outcomes (patient-reported)

a. Global assessment of change. The Patient Global Impression of Change scale (PGIC [88]) will be used to evaluate participants' overall evaluation of the impact of their A/C treatment.

b. Work-related impairment. Three questions about work/disability status and missed work due to CMP will be adapted from the National Health Information Survey (NHIS) [89].

c. Depression severity. Using the Personal Health Questionnaire (PHQ-8) [90,91], we will measure depression severity. The PHQ-8 is established as a valid screener and severity measure for depressive disorders in large clinical studies [90,92-94]. Baseline depression will also be examined as a possible moderator of outcome.

d. Anxiety. The 2-item Generalized Anxiety Disorder Scale (GAD-2) [95,96] will be used to screen for anxiety disorders. The GAD-2 has been used to detect anxiety disorders in primary care and has well established psychometric properties. Baseline GAD-2 scores will also be examined as another possible moderator of outcome.

e. Quality of life/health utility. The SF Health Survey (SF-12v2) [97] will be used to measure quality of life. The SF12 is a widely used and well-validated generic measure of functioning that is a recommended IMMPACT measure for examining functioning (this will also be used as a health utility measure) [82].

f. Patient satisfaction. Finally, participant satisfaction with services provided by the health plan (allopathic providers) (0 = worst health care possible, 10 = best health care possible) will be assessed as well as satisfaction with A/C provider when pertinent [98]. We will also use the practitioner skill subscale from a self-report outcome measure designed for assessing CAM treatments [99,100].

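### PGIC is described as rating A/C treatment but is compared with patients who by design receive none, and the common quadratic time model is not identifiable for patient satisfaction

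*Protocol article*

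**What the plan says.** In the protocol article, item a of Secondary outcomes (patient-reported) states that PGIC "will be used to evaluate participants' overall evaluation of the impact of their A/C treatment". Table 5, under Secondary Outcomes (survey instruments), has the row "Patient global impression of change" ticked at months 1, 3, 6 and 12, with nothing at month 0 and no restriction to A/C users. The row "Patient satisfaction" is ticked at months 1 and 3 only. Item f of the same outcomes section limits satisfaction with the A/C provider to participants for whom it applies, while satisfaction with health-plan care is asked of everyone. PGIC carries no such limit.

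Phase 3 Data Analysis, Patient-reported outcomes, sets multilevel modeling "to examine differences across time in primary (pain intensity/interference/bothersomeness) and secondary patient-reported outcomes between A/C users and matched comparison participants". On time, it says: "Two parameters (linear and quadratic slope) will characterize change across time". The occasions are named as well: "the quadratic model for time (baseline and 1-, 3-, 6-, and 12-month follow-ups) captures nonlinear change across time". The only flexibility by outcome concerns the distribution: "Depending upon the distribution, normal, logistic, or Poisson models will be used". No outcome is exempted from the time terms.

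The Phase 3 overview describes comparison patients as not receiving A/C. Phase 3 Sample Size plans 200 acupuncture and 200 chiropractic index participants with two matched comparison participants each, 1,200 in all.

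**The concern.** There are two separate faults.

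The first is about what PGIC measures. Its stated purpose presupposes that the respondent has had A/C. The planned contrast sets those respondents against patients who, by design, have not. If the item is put as described, index participants give an opinion of a treatment, and comparison participants either cannot answer or answer about something else. The difference between groups would then mix change in the pain condition with opinion of A/C. Nothing in the analysis could separate the two, and answers already collected under an A/C-specific stem could not be converted afterwards. PGIC is the only listed outcome in which patients give their own overall verdict on change.

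The second is about the analysis. A time model built for five occasions is applied without exception to outcomes on other schedules. For satisfaction the stated model cannot be fitted in full. For PGIC it can be fitted, but the parameters no longer mean what the text says. Satisfaction is not incidental: the overarching goal in the Study Overview and the planned Phase 3 group comparison both name it.

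**Working it through.** **Plan's own figures.** Index participants: 200 + 200 = 400. Comparison participants: 2 × 400 = 800. Total: 400 + 800 = 1,200, as stated. The power statement also reproduces. With SD 2 and correlation 0.5, the SD of change is 2 × √(2 × (1 − 0.5)) = 2.0. For a 1-unit difference, 100 per group and two-sided alpha 0.025, power is 90.2% (normal approximation) or 89.8% (noncentral t). It rests on the BPI and is not touched by this point. The article gives no figure for PGIC or satisfaction.

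**Share without A/C, by design.** 800 / 1,200 = 66.7%. This is an allocation, not an observed proportion. The section on identifying comparison participants expects that some of them may report A/C use. Index participants enter on a referral, and the Phase 2 focus-group section recognises patients who were referred but did not take it up. The article gives no rate for either, so the realised share cannot be computed.

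**PGIC, texts side by side.**
- Purpose: rates the impact of the participant's own A/C (outcomes section, item a).
- Population: all patients at four follow-ups (Table 5).
- Contrast: A/C users against matched comparison patients (Phase 3 Data Analysis).
- The second and third agree with each other. The first fits only A/C users. The limit that would resolve this is attached to A/C-provider satisfaction but not to PGIC.

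**Identifiability of the time model.** Fixed effects per group are (1, t, t²). With two groups and group-by-time terms there are 6 coefficients. Each group needs at least 3 distinct occasions.

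| Outcome | Months | Occasions | Rank of design |
|---|---|---|---|
| Full schedule | 0, 1, 3, 6, 12 | 5 | 6 of 6 |
| PGIC | 1, 3, 6, 12 | 4 | 6 of 6 |
| Satisfaction | 1, 3 | 2 | 4 of 6 |

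For satisfaction the rows per group are (1, 1, 1) at month 1 and (1, 3, 9) at month 3. The polynomial (t − 1)(t − 3) = t² − 4t + 3 is zero at both months, so any multiple of it can be added to a group's curve without changing the fit. The linear and quadratic slopes therefore cannot be separated. Any two occasions give the same result, so it does not depend on which two columns of the extracted table hold the ticks.

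**What the PGIC slopes mean.** PGIC has no month-0 value and is already a rating of change. Its fitted curve describes how perceived change runs from month 1 to month 12. It does not describe change from baseline, and an intercept at month 0 would be an extrapolation. With one observation per occasion and equal independent errors, the variance factor of that intercept is 1.79 on PGIC's four occasions, against 0.64 on the full five.

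**The case against.** The strongest reply is that item a is a one-line description and not the questionnaire stem. It names an existing scale, no item text is shown, and the Phase 2 section says that questions belonging to validated instruments will be left unchanged. An A/C-specific stem is therefore less likely, though the article does not expressly call PGIC validated. This stands in part: one cannot say that the groups will in fact be asked different questions. It does not remove the conflict. If a neutral stem is intended, item a misstates the outcome; if an A/C stem is intended, the group comparison fails. Either way the text has to be reconciled.

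The second reply is that a condensed article may leave to the full analysis plan the dropping of a term that cannot be estimated for one secondary outcome. That limits the weight of the satisfaction point, since no result would be distorted silently and a simpler comparison is at hand. But the article does not leave the model open. It fixes the time terms for all these outcomes, and for satisfaction that statement is wrong.

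Three stronger readings are tempting, and the document does not support them:
- A reader might infer that the quadratic model cannot be fitted to PGIC either. It can: four occasions identify all six coefficients.
- A reader might take 67% as the proportion who will actually have no A/C to rate. It is the design share only.
- A reader might infer that the PGIC rating would favour A/C. The Background mentions expectation effects in controlled trials, but nothing in the article gives a direction or size of bias for PGIC.

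**Conclusion.** The point holds on two counts. The stated purpose of PGIC does not fit the population and contrast set for it. If it is administered as described, the comparison is not interpretable, and by design this concerns 800 of 1,200 participants, subject to crossover and to referrals not followed through. The common time model is not identifiable for satisfaction, with rank 4 of 6 on two occasions. For PGIC the remaining point is one of interpretation: the model is estimable, but its slopes do not measure change from baseline.

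The PGIC conclusion is conditional on the description in item a reflecting the item as asked, because the stem is not shown. The satisfaction conclusion rests on Table 5 scheduling it at only two occasions. Both counts concern secondary outcomes. The BPI and bothersomeness outcomes and the sample size are unaffected. The point should be corrected before Phase 3 begins, but it does not threaten the main comparison.

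**What to change.** 1. Reword item a so that PGIC asks every participant about overall change since the baseline assessment, without naming A/C, and use the same stem in both groups. Alternatively, restrict PGIC to A/C users, mark this in Table 5, and drop it from the between-group comparison.
2. State that PGIC is analysed on months 1, 3, 6 and 12 without a baseline occasion, and that its time terms describe the course of perceived change from month 1.
3. Compare satisfaction with health-plan care at months 1 and 3 by visit, or with a two-occasion model without a quadratic term.
4. Report satisfaction with the A/C provider descriptively, in A/C users only.

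The cost is a change to one questionnaire stem and a few sentences of analysis text, with no added assessments. Phase 2 already plans to refine the questionnaires before Phase 3. The small downside is that a neutrally worded PGIC no longer isolates perceived impact of A/C; a separate item for index participants can capture that.
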